### Randomisation

A statistician who will not be involved in recruitment and will be blinded to the identity of participating GPs will allocate GP clusters to either the intervention or the control arm. Randomisation will be performed as stratified randomisation using a minimization procedure. Stratification factors are state, clinic size (GP equivalent full time >5 (yes/no)), and location (urban vs regional/rural). We will randomise clinics in blocks of two, or every 2 weeks, whichever occurs first.

### Intervention

#### Intervention components

The intervention components have been co-designed by the research team, an Intervention Advisory Group comprising policy and practice representatives, and a key non-government mental health organisation *Beyond Blue* and piloted by a GP reference group. A steering group comprising key practice and policy representatives from across Australia reviewed the intervention design and provided advice to enhance its usability and sustainability. This approach was used to ensure that GPs receive an intervention that is relevant to their clinical practice as well as relevant to policy contexts.

Academic detailing will be provided in a single online session using video-conferencing. The session will be led by a GP opinion leader along with a professional academic detailer. GP opinion leaders are GPs having been nominated by compensation scheme partners as these GPs are well versed in the complexities of the workers’ compensation system but are not representatives of the compensation schemes themselves. Each GP opinion leader will be supported by an experienced academic detailer who has expertise in providing educational outreach programs to GPs. GPs from clusters in the intervention arm of the trial will be detailed on how to improve care for patients with work-related mental health conditions in accordance with the guideline. The format of each session will include (1) introduction to the guideline and the provision of statistics about work-related mental health conditions; (2) discussion of the key challenges that are faced by attending GPs; and (3) discussion of a case study with advice and instruction on how to implement guideline-concordant care. During the academic detailing session, opinion leaders will invite GPs to join the digital community of practice, enrol them as members of this community, and provide a demonstration on how to navigate and use the digital community of practice platform. Opinion leaders will keep a log of the key challenges and issues reported by GPs at each detailing session and this log will be used to inform the content of the community of practice and contribute to the process evaluation. To ensure fidelity of the academic detailing, all academic detailing sessions will be recorded. A random selection of 20% of sessions will then be assessed against a pre-determined checklist, adapted from Carroll et al. [35] for academic detailing sessions, and a fidelity score will be reported. In addition, a qualitative and quantitative fidelity assessment will be used to assess the fidelity of the first five academic detailing sessions and provide feedback to GP opinion leaders on the delivery of these sessions.

The digital community of practice is an online platform that will showcase the guideline recommendations and provides avenues to discuss and support guideline implementation strategies. A central component of the platform will be a discussion forum. In addition, the platform will offer a range of regular content in the form of webinars, case discussions, and news. A content roster and engagement protocol will also be used to facilitate ongoing engagement. The content roster will be reviewed quarterly to adjust for ongoing developments in published educational materials or other resources, and in response to GP engagement levels over the preceding quarter. Once GPs are enrolled into the digital community of practice, they will continue to have access to the community of practice for the duration of the trial (until September 2022).

Participating GPs will be provided with resources including the full guideline, flowchart of guideline recommendations, and a checklist of clinical indicators that was created by the expert Guideline Development Group during development of the guideline. They will also be supplied with resources from the compensation partners and *Beyond Blue*, a prominent non-government mental health organisation in Australia*.*

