### Setting

The study will be conducted across all states and territories in Australia. Recruitment of GPs will occur from December 2020 until December 2021 whilst recruitment of patients will occur from February 2021 until September 2022 or the latest date representing nine-months after the final GP provides baseline measures.

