#### Control group

Participating GPs in clinics assigned to the control group will receive no support for guideline implementation. At the conclusion of the trial, GPs in the control group will be invited to attend an academic detailing session and engage in selected activities from the community of practice.

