#### Secondary outcomes

Secondary outcomes will capture the effect of the intervention on patient health status and work participation. Patient health status will be measured using the short-form 36-item version 2 (SF-36 v2) [38] and the Depression and Anxiety Stress Scale-21 item (DASS-21) [39]. Work participation will be measured using the return to work items within the Australian National Return To Work Survey [40].

The SF-36 v2 provides measures for mental health symptoms and function, as well as measures of physical function [38]. Since patients with work-related mental health conditions are likely to experience both psychological and physical ill health, the SF-36 v2 is an appropriate measure to assess health status [41]. Due to heterogeneity in the mental health conditions experienced by participating patients, it is necessary to use a broad measure of health that is capable of measuring changes in psychological health. The SF-36 v2 Mental Component Score and Mental Health Domain Score are strongly correlated with measures for depression, anxiety, post-traumatic stress disorder, and substance use [42], which are common work-related mental health conditions. The SF-36 v2 is also sensitive to change following intervention.

The DASS-21 assesses the presence and severity of the core symptoms of depression, anxiety, and stress [39]. Accordingly, the DASS-21 allows not only a way to measure the severity of a patient’s symptoms but a means by which a patient’s response to treatment can also be measured. The National Return To Work survey has been used by the Australian government for over 18 years to assess level of work participation for people who are working and those who are not [40].

Patient endpoints are at the time of their initial appointment with the GP (T0, baseline) and every 3 months after that for 9 months. Patients will be provided paper or electronic links to relevant surveys (including specific measures of psychological disorder) or they will be able to provide their responses via a structured telephone interview, as per their preference. Data for both GP and patient outcomes will be collated electronically using REDCap [43].

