#### Secondary analysis

*Patient analyses*: Using a similar mixed model approach as in the main analyses, changes in patient health status (using the SF-36 v2), and work participation (using relevant measures of the National Return To Work Survey) will be measured by comparing the scores on patient surveys from baseline to 3, 6, and 9 months following their initial GP consultation.

*Adjusted analyses*: The main analysis and subgroup analyses above include adjustment for the stratification factors, which are state, clinic size (GP equivalent full time >5 (yes/no)), and location (urban vs regional/rural), additional mental health training.

*Missing data*: As the GP and patient-level data are longitudinal samples, a missing data analysis will be done on each longitudinal data set and investigations made for predictors of missingness. These investigations will examine the effect of key demographic and other factors particularly on the presence of missing outcomes. If outcome data is found to not be missing at random, then multiple imputation will be applied using the predictors for missingness.

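### The stated trial end, September 2022, falls about nine months before the last patient surveys, so the dates could allow control GPs to receive the intervention during patient follow-up

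*Protocol article*

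**What the plan says.** Five places in the protocol article bear on this.

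- **Intervention components.** Once GPs are enrolled in the digital community of practice, they keep access to it "for the duration of the trial (until September 2022"). This is the only place where the end of the trial is given a date.
- **Control group.** "At the conclusion of the trial, GPs in the control group will be invited to attend an academic detailing session" and to take part in some community-of-practice activities. No date is attached. Until then, control GPs get no implementation support.
- **Setting.** "Recruitment of GPs will occur from December 2020 until December 2021", and "recruitment of patients will occur from February 2021 until September 2022 or the latest date representing nine-months after the final GP provides baseline measures".
- **Secondary outcomes.** Patients are surveyed at their initial appointment and "every 3 months after that for 9 months".
- **Secondary analysis.** All three follow-up times are used, by "comparing the scores on patient surveys from baseline to 3, 6, and 9 months following their initial GP consultation".

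Nothing in the article shortens follow-up for late recruits, closes patient recruitment earlier, or ties the control-arm offer to the last patient survey.

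**The concern.** September 2022 is both the stated end of the trial and the stated (earliest) close of patient recruitment. A patient who enters at that close still has the whole 9 months of surveys to come. If the control-arm offer is triggered by the stated trial end, some control patients would be under the care of GPs who have been offered detailing while those patients are still being measured. On the other side, intervention GPs are promised the platform only up to the same date. Both effects would tend to shrink late differences between the arms.

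At stake are the patient health and work participation comparisons, mainly at 6 and 9 months, and the parts of the economic evaluation built on patient data: QALYs, medical costs and productivity.

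**Working it through.** **Inputs.** GP recruitment December 2020 to December 2021; patient recruitment February 2021 to September 2022 (Setting). GP outcome at baseline and 9 months (Primary outcome). Patient surveys at 3, 6 and 9 months (Secondary outcomes). Seven patients per GP expected over 9 months, and 448 patients with 3-month data (Sample size).

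**1. Reproducing the stated end date.** Last GP baseline + 9 months = December 2021 + 9 months = September 2022. The date matches the last GP assessment, so the primary outcome is complete by then.

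**2. The same step for patients.** For a patient enrolled in September 2022:
- 3-month survey: December 2022
- 6-month survey: March 2023
- 9-month survey: June 2023

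Patient follow-up therefore ends about 9 months after the stated end of the trial, and later still if the alternative recruitment limit under Setting applies.

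**3. Could follow-up simply stop in September 2022?** The Sample size section suggests not. It counts 64 × 7 = 448 patients, recruited within 9 months, as having 3-month data. A clinic entering in December 2021 recruits until September 2022, and its last patients reach 3 months in December 2022.

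**4. Share of surveys dated after September 2022.** The article does not give the accrual pattern, so two assumptions are shown.

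*Assumption A: patients accrue evenly over the 20 months from February 2021 to September 2022.* The share at month m is m/20.
- 9 months: 9/20 = 45%
- 6 months: 6/20 = 30%
- 3 months: 3/20 = 15%

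*Assumption B: GPs enter evenly over 12 months and each recruits evenly for 9 months.* Let a be the months from a GP's entry to the end of GP recruitment, and b the months from a patient's entry to the end of that GP's recruitment. The survey at month m is late when a + b < m. The share is (m²/2)/(12 × 9).
- 9 months: 40.5/108 = 37.5%, about 38%
- 6 months: 18/108 = 16.7%, about 17%
- 3 months: 4.5/108 = 4.2%, about 4%

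**5. How much of the follow-up lies after that date.** Among patients whose 9-month survey is late, the time between September 2022 and that survey runs from 0 to 9 months. Its mean is 9/2 = 4.5 months under A. Under B, a + b has density proportional to its value on 0 to 9, hence mean 6, so the mean late time is 9 − 6 = 3 months.

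**The case against.** The best defence is that the Control group section carries no date. The conclusion of a trial ordinarily means the end of data collection, and the September 2022 date sits in a parenthesis about platform access. On that view the sponsor always meant to wait for the last patient. This stands in part: a reader might infer that the article plans to treat controls during follow-up, and it does not say so. Crossover follows only from reading the two sections together. But the intended reading would contradict the one date given for the trial's duration, and platform access would still be assured only until September 2022 while intervention patients were in follow-up. The sections need reconciling either way.

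A second objection concerns size, and it stands. Even accrual over 20 months ignores staggered GP entry. Assumption B respects that and lowers the shares, most of all at 3 months, the only time for which patient-level power is stated. B is itself an assumption, because the article does not strictly limit each GP to 9 months of recruitment.

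A reader might also multiply the standardised effect of 0.5 by the unaffected 9-month share, 0.5 × (1 − 0.45) = 0.275, and conclude that the effect would nearly halve. The documents do not support that. The 0.5 is given for 3 months. The offer is an invitation with unknown uptake. A survey in October 2022 may follow about 8 of 9 months of unaffected care.

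Finally, the article assures platform access until September 2022; it does not say that the platform then closes. Detailing and resources already delivered are not undone.

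**Conclusion.** The inconsistency is real: the stated trial end fits the last GP assessment and not patient follow-up, which on the stated dates runs to about June 2023. As written, the dates could allow control GPs to receive the intervention, and leave intervention GPs without assured platform access, before the patient surveys are complete.

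The surveys dated after September 2022 would be about 38–45% of those at 9 months, 17–30% at 6 months and 4–15% at 3 months, the range reflecting the two assumed recruitment patterns. These are shares of surveys that could be exposed, not estimates of bias. The direction is towards no effect; the amount cannot be derived from the article.

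A reader might extend the point to the whole trial. That would be wrong. GP concordance, which is the primary outcome and also the primary outcome of the economic evaluation, is measured by September 2022 on the planned GP recruitment dates. Only patient health, work participation, QALYs and patient-level costs are concerned.

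**What to change.** Reconcile Setting, Intervention components, Control group and Secondary outcomes. Define the conclusion of the trial as the date of the last patient's 9-month survey, and use that definition for both the control-arm offer and the end of community-of-practice access. Replace the fixed September 2022 date accordingly, since the recruitment limit under Setting can itself move.

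The change is one of wording. Its cost is that control GPs wait up to about 9 months longer for the offer and the platform has to be kept open for that time.

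If the calendar cannot move, keep all patient surveys in the main analysis and add a prespecified sensitivity analysis that leaves out, in both arms, those dated after the control-arm offer. Leaving them out of the main analysis would not be a good trade: with an offer in September 2022, it could discard about 38–45% of the 9-month data to remove a dilution of unknown size.

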#### Control group

Participating GPs in clinics assigned to the control group will receive no support for guideline implementation. At the conclusion of the trial, GPs in the control group will be invited to attend an academic detailing session and engage in selected activities from the community of practice.

### Outcomes

#### Primary outcome

The primary outcome is concordance with guideline recommendations by participating GPs. Guideline concordance will be assessed at baseline and 9 months later using virtual simulated patient scenarios. At each data collection point, GPs will be presented with three virtual scenarios of varying levels of complexity and patient circumstance. The three virtual scenarios for each GP at each data collection point will be randomly selected from a set of eighteen virtual scenarios, controlling for learning effects and order effects, and balancing rigorous measurement with participation burden. We based the development of these scenarios on 20 interviews with patients who have lived experiences of work-related mental health conditions to ensure that virtual scenarios reflect the range of patient characteristics that a GP would see.

This approach has been used previously to evaluate practice and as an educational tool in compensable injury research with GPs in Europe [36] and with physiotherapists in Australia [37]. The virtual scenarios are approximately 15 min duration each and focussed on typical presentations to GPs by patients with work-related mental health conditions. Each virtual scenario includes a short video of a simulated patient who describes their symptoms, circumstances and context. Participating GPs are then prompted to respond to questions about how they would assess, diagnose, and manage the patient in the virtual scenario.

Guideline-concordant responses to the scenarios will be measured using a tool that reflects the checklist of indicators that have been included in the Guideline. Responding to each set of three virtual scenarios can result in a best score of 9 or a worst score of 0. The tool was pilot tested with three groups: (1) GPs who are experts in the Guideline, (2) GPs who are not familiar with the Guideline, and (3) medical and research students who have no clinical general practice expertise. The tool was found to have a scale reliability score of Cronbach’s *α*=0.74.

#### Secondary outcomes

Secondary outcomes will capture the effect of the intervention on patient health status and work participation. Patient health status will be measured using the short-form 36-item version 2 (SF-36 v2) [38] and the Depression and Anxiety Stress Scale-21 item (DASS-21) [39]. Work participation will be measured using the return to work items within the Australian National Return To Work Survey [40].

The SF-36 v2 provides measures for mental health symptoms and function, as well as measures of physical function [38]. Since patients with work-related mental health conditions are likely to experience both psychological and physical ill health, the SF-36 v2 is an appropriate measure to assess health status [41]. Due to heterogeneity in the mental health conditions experienced by participating patients, it is necessary to use a broad measure of health that is capable of measuring changes in psychological health. The SF-36 v2 Mental Component Score and Mental Health Domain Score are strongly correlated with measures for depression, anxiety, post-traumatic stress disorder, and substance use [42], which are common work-related mental health conditions. The SF-36 v2 is also sensitive to change following intervention.

The DASS-21 assesses the presence and severity of the core symptoms of depression, anxiety, and stress [39]. Accordingly, the DASS-21 allows not only a way to measure the severity of a patient’s symptoms but a means by which a patient’s response to treatment can also be measured. The National Return To Work survey has been used by the Australian government for over 18 years to assess level of work participation for people who are working and those who are not [40].

Patient endpoints are at the time of their initial appointment with the GP (T0, baseline) and every 3 months after that for 9 months. Patients will be provided paper or electronic links to relevant surveys (including specific measures of psychological disorder) or they will be able to provide their responses via a structured telephone interview, as per their preference. Data for both GP and patient outcomes will be collated electronically using REDCap [43].

### Economic evaluation

The economic evaluation will take a societal perspective in quantifying the additional costs (savings) and health gains associated with the intervention within the trial period. The primary outcome for the economic evaluation will be GP concordance with guideline recommendations. The secondary outcome for the economic evaluation will be quality-adjusted life-years (QALYs) in participating patients; calculated based on SF-36 v2 data at each time-point [44] and using an area-under-the-curve approach.

The cost analysis will capture direct costs of the intervention and control conditions (based on project records and fidelity data), medical costs during the trial period, and productivity gains during the trial period. Medical costs will be estimated based on patient-level administrative data from the Medicare Benefits Scheme (MBS), from Pharmaceutical Benefits Scheme (PBS), and from workers’ compensation schemes (for those patients who submit a claim and provide consent for data access), plus patient self-report of health service use funded by other payers (e.g. hospitalisations and allied health care). Productivity gains will be estimated based on patient-level data regarding return to work from the National Return To Work Survey items. Results of the economic evaluation will be expressed as cost per point improvement in concordance with the Guideline, and cost per QALY gained.

### Realist evaluation

A realist evaluation of the intervention will be conducted using three methods: a knowledge, attitudes, and practice questionnaire provided to GPs at baseline and 9 months later, interviews with a random sample of 20 GPs and 20 participants upon completion of the intervention, and qualitative analysis of the social interactions on the community of practice. All decisions, tailoring and modifications to the structure, format, content, or design of the community of practice will also be documented in a log book.

### Planning for sustainability

A stakeholder workshop will be held to identify how the intervention can be sustained following completion of the trial. Outcome data from the intervention, economic evaluation, and process evaluation will be presented for consideration and reflection by participants.

### Blinding

Given that the intervention involves active engagement with GPs, it is inevitable that GPs will become aware of their group allocation as the study progresses. Patients, however, will not be informed about whether their GP clinic has received the intervention. Clinical trial coordinators will be blinded to the group allocation during quantitative and qualitative data collection; however, it is possible that they will be able to identify a GP’s allocation by the content of their conversations. The study project officer and research assistant will be involved in coordinating and delivering the intervention and will, therefore, not be blinded to group allocation. All GP and patient data will be de-identified by the research assistant before analysis for the primary outcome.

